### Secondary outcomes

The secondary outcomes are:Women’s level of self-efficacy at 34 weeks, assessed with the General Self-Efficacy scale [24]Pregnancy weight gain assessed by gain in weight between recruitment and 34 weeks gestationMaternal diet quality one month after birthBreastfeeding status one month after birth (yes/no)Neonatal whole body bone mineral content (BMC), lean and fat mass within 2 weeks after birth assessed by dual-energy X-ray absorptiometry (DXA).

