### Neonatal DXA

Infants receive DXA scans within the first 2 weeks after delivery. The reliability of DXA measurements in neonates has been demonstrated in the Southampton Women’s Survey [2]. The baby is pacified, fed, fully undressed and then swaddled in a towel before being placed on the densitometer (Hologic Discovery instrument using paediatric software (Hologic Inc., Bedford, MA, USA)). The scanner is calibrated against a spine phantom every day together with daily quality assurance and step-wedge calibration, performed as per manufacturer’s instructions (Hologic Inc., Bedford, MA, USA). If possible, the baby is scanned while still an inpatient. If this is not possible, the mother and baby return for assessment within 14 days of birth. Whole body and lumbar spine bone area, bone mineral content and bone mineral density are measured. The infant DXA assessments are associated with a low dose of radiation exposure, roughly equivalent to 2 days of background radiation in Cornwall (UK) and 7 days in other parts of the UK.

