### Statistical analyses

We will perform a complete case analysis for each outcome using *t* tests to compare the two primary outcomes between the relevant intervention arms. Multiple linear regression will be used to adjust for any differences identified at baseline. Similar analyses will be conducted for the secondary outcomes. The neonatal bone and body composition analyses will include stratification by season of birth in light of recent findings from the MAVIDOS trial [10]. We will also conduct exploratory analyses of the interaction between HCS and vitamin D on both primary outcomes. For binary outcomes, chi-squared tests or Fisher’s exact test for rare outcomes will be used. To adjust for imbalances at baseline, logistic regression will be used, or for rare outcomes, binary regression or Poisson regression with robust variance.

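### The covariate rule for the neonatal DXA outcomes does not bring in infant sex or age at scan, so these comparisons are probably less precise than they need be

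*Protocol article*

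**What the plan says.** The Statistical analyses section of the protocol article sets one approach for continuous outcomes: "We will perform a complete case analysis for each outcome using *t* tests to compare the two primary outcomes between the relevant intervention arms". Its covariate rule is "Multiple linear regression will be used to adjust for any differences identified at baseline". It then adds "Similar analyses will be conducted for the secondary outcomes", and for the neonatal bone and body composition analyses it names one extra element, stratification by season of birth.

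The Secondary outcomes section lists whole body bone mineral content (BMC), "lean and fat mass within 2 weeks after birth". The Neonatal DXA section sets the timing: "If possible, the baby is scanned while still an inpatient", and "If this is not possible, the mother and baby return for assessment within 14 days of birth".

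Infant sex, age at scan and gestation at birth are not named as covariates anywhere in the article.

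**The concern.** BMC, lean mass and fat mass are absolute quantities. The scan window mixes babies measured during the hospital stay with babies brought back as late as day 14. If these quantities shift over the first two weeks, or differ between boys and girls, the spread within each arm includes variation unrelated to either intervention. Both effects are general knowledge about newborns; the article states neither.

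The covariate rule does not remove this variation, for two reasons. Age at scan does not exist at baseline. Infant sex is fixed by then, but it is not among the variables that the Early pregnancy section collects, all of which describe the mother. In addition, the rule picks covariates by observed imbalance, not by how strongly they predict the outcome, so it is not designed to gain precision.

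At stake are wider confidence intervals for three secondary outcomes, and covariate choices left open in an analysis for which the authors did specify season.

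**Working it through.** **Inputs from the Sample size and power calculation section:** 300 v 300 per marginal comparison, alpha 0.025, a difference of 0.25 SD, 80% power. These figures are for the two maternal primary outcomes. The article gives no power and no expected number of scans for DXA.

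**Assumptions:** the share of variance explained (R²), two-sided alpha 0.05 for a secondary outcome, and 300 v 300 infants scanned.

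**1. The plan's own figure.** Standard error in SD units = √(2/300) = 0.0816. Then 0.25/0.0816 = 3.062. Power at two-sided 0.025 = Φ(3.062 − 2.241) = 79.4%, which reproduces the stated 80%.

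**2. Effect of adjustment.** The standard error is multiplied by √(1 − R²). The equivalent number per side is 300/(1 − R²). The difference detectable with 80% power at alpha 0.05 is (1.960 + 0.842) × 0.0816 × √(1 − R²).

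| Assumed R² | SE ratio | Equivalent n per side | Detectable difference (SD) | Power at 0.25 SD, 300 v 300 | Power at 0.25 SD, 200 v 200 |
|---|---|---|---|---|---|
| 0 | 1.000 | 300 | 0.229 | 86.5% | 70.5% |
| 0.05 | 0.975 | 316 | 0.223 | 88.1% | 72.7% |
| 0.10 | 0.949 | 333 | 0.217 | 89.8% | 75.0% |

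The last column assumes that fewer infants are scanned.

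**3. Is an R² of 0.05–0.10 plausible?** Take the residual SD as 1.
- Sex, balanced, with a difference d: explained variance d²/4. An assumed d of 0.2 to 0.5 SD gives 0.010 to 0.0625, so R² alone is 0.01 to 0.06.
- Age at scan, uniform over 14 days, with drift b per day: explained variance (14b)²/12. An assumed b of 0.02 to 0.10 SD per day gives 0.0065 to 0.163, so R² alone is 0.007 to 0.14.
- Both together, taken as independent: 0.0165/1.0165 = 0.016 at the low end and 0.226/1.226 = 0.18 at the high end. The SE reduction is then 1 − √0.984 = 0.8% to 1 − √0.816 = about 10%.

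The range 0.05–0.10 lies inside these limits, but the limits are themselves assumptions. Because inpatient scanning is preferred, ages will probably not be uniform, and the true spread could be smaller or larger.

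**4. HCS scan timing.** If mean scan age differed by 2 days between arms (assumed), the same drift would give a spurious difference of 2 × 0.02 = 0.04 SD to 2 × 0.10 = 0.20 SD. Nothing in the article shows such a gap.

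**The case against.** The strongest objection is scope. This is a condensed article, and a full covariate list for a secondary outcome is often left to the analysis plan. Saying that the analyses will include season stratification does not exclude other covariates. This stands as a reason to rate the point low, and if the analysis plan already names sex and age at scan, the point is met. It does not remove the point, because the article does fix a covariate rule and does single out these outcomes for special handling.

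Second, the premises and every R² value come from outside the article. That also stands: the size is a range under assumptions.

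Third, age at scan arises after randomisation and depends partly on the length of the postnatal stay, so adjusting for it needs a reason. The reason is that it records when the measurement was taken. It should be stated as such, with the result without it shown alongside. Infant sex is settled before recruitment and raises no such difficulty.

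Three stronger readings are tempting, and the article does not support them.
- **That the DXA outcomes are compared raw and a vitamin D effect is hidden.** Season stratification is planned and regression for baseline differences carries over. Vitamin D is randomised and double blind, so leaving out prognostic covariates causes no bias and does not inflate type I error. The assumed gain in power is 1.6 to 3.3 points.
- **That the HCS comparison is biased by scan timing.** The Healthy Conversation Skills support section does give each arm its own nurses, and staff are not blind to that allocation. But the section on admission for labour says only that a research nurse arranges the scan, without tying that nurse to an arm.
- **That the gain is nearer 11%, or 75 infants per side.** That needs an assumed R² of 0.20 (√0.80 = 0.894; 300/0.80 = 375) reached by adding gestation at birth, which supplementation might affect and which should stay out of the main model.

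**Conclusion.** The point holds as a minor matter of efficiency. The stated rule leaves out age at scan by construction and infant sex in all likelihood, while scans may fall anywhere in a 14-day window. Naming the two covariates in advance is a better method at almost no cost.

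With 300 v 300 infants and an assumed R² of 0.05–0.10, standard errors fall by about 2.5–5%, and power at 0.25 SD (two-sided alpha 0.05) rises from 86.5% to between 88.1% and 89.8%. If the covariates explain less, the gain could be under 1%. The vitamin D comparison is valid as planned. For HCS, a timing difference is worth checking but should not be presumed. No primary outcome is affected.

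**What to change.** In Statistical analyses, state that whole body BMC, lean mass and fat mass are analysed by linear regression on allocation, with infant sex and age in days at scan as prespecified covariates beside season of birth. Describe age at scan as a measurement-timing variable. Report the result without it, and mean age at scan by arm for both factors. Add gestation at birth only in a sensitivity analysis, because treatment might affect it. Fix this before unblinding.

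The cost is a sentence or two, two degrees of freedom, and a main model that conditions on one post-randomisation timing variable. Birth and scan dates should already be held, since season of birth and the 14-day limit require them; that infant sex is recorded is an inference.

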### Process evaluation

In accordance with Medical Research Council (MRC) guidance, our process evaluation will assess implementation, mechanisms of action and context [27]. It runs throughout the trial. We have involved stakeholders, including maternity and public health practitioners and members of a lay advisory panel, in the development of a logic model which describes the way in which the intervention processes will bring about change in the outcomes. Implementation is being assessed through observation and recording of staff interactions with participants and includes an assessment of Healthy Conversation Skills research nurses’ competence in the skills they have been taught and their confidence in the use of these skills. Recruitment and retention of participants will be monitored throughout the trial. Mechanisms of action will be assessed through interviews with women to find out their experiences of taking part in the trial and, in particular, their experiences of contact with nurses trained in Healthy Conversation Skills. We will also examine intermediate outcomes, as we hypothesise that change in diet will be facilitated by improvements in women’s self-efficacy. In assessing context, we will aim to identify any factor that might act as a barrier or facilitator to intervention implementation or effects and will carry out detailed mapping of local services and national policy that might influence the delivery and efficacy of the intervention.

### Ethical considerations

Information sheets are given to participants outlining the procedures that they will undergo, and plain English is used to facilitate participants’ understanding of the study. Participants also have opportunities, at each follow-up appointment, to discuss any concerns with study staff. The infant DXA assessments are associated with a low dose of radiation exposure, roughly equivalent to 2 days of background radiation in Cornwall (UK) and 7 days in other parts of the UK including Southampton. The dose of vitamin D supplementation has been chosen to bring women just into the normal range (>50 nmol/l circulating 25-hydroxy vitamin D), to avoid elevating to supranormal levels. This approach is consistent with that taken in the MAVIDOS trial of vitamin D supplementation during pregnancy [10]. Previous observational studies in Southampton have suggested low risk of adverse effects from vitamin D supplementation: data from the Princess Anne Cohort study showed a small excess of atopic asthma in children born to mothers with the highest levels of vitamin D in pregnancy [28]. However, numbers of children affected were lower than expected from general population prevalence, and the confidence intervals around the association were wide. No associations between atopy in infancy and high levels of maternal vitamin D have been shown in the Southampton Women’s Survey, and other studies have suggested neutral or negative associations [29–31].

Blood and tissue samples will be processed for storage on the day of collection and will be stored in freezers in the MRC Lifecourse Epidemiology Unit, Southampton General Hospital. They will be stored until all analyses are completed. [name], Director of the Unit and chief investigator for the SPRING trial, will have custodial responsibility, and the samples will be stored in compliance with Human Tissue Authority (HTA) regulations.

There is a potential risk of distress with any interview. Staff will be trained in interviewing techniques and will terminate an interview in the rare event that questions cause participants distress. If a participant should become distressed, she will be reminded of the helpline number and will be referred to support services, a list of which will be available in the research clinic.

### Reporting of adverse events

#### Anticipated adverse events

Some pregnancy-associated complications are expected to arise spontaneously during the study and are not associated with vitamin D supplementation. These include cholestasis of pregnancy, pregnancy-induced hypertension, gestational diabetes, pre-eclampsia, eclampsia, premature labour or delivery, instrumental delivery, Caesarean section, miscarriage or stillbirth.

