## Background

The nutritional status and health of mothers influence the growth and development of infants during pregnancy and postnatal life [1]. Growth and development at these stages of the lifecourse will influence the risk of non-communicable diseases such as cardiovascular disease and obesity in adulthood. Interventions that focus on improving the nutritional status and lifestyle of mothers have the potential to optimise the growth and development of the fetus as well as improve the health of mothers themselves. Studies have shown that maternal nutrition influences child body composition [2, 3]. There are two principal approaches to improving the nutritional status of pregnant women: nutritional supplementation (multiple-micronutrient supplementation as well as single vitamin supplements to correct deficiencies) or behaviour change interventions that aim to improve the diet quality of pregnant women [4]. Improving the diets of women of childbearing age is likely to require complex interventions that are delivered in a socially and culturally appropriate context [5].

Multiple-micronutrient approaches have improved maternal and birth outcomes in studies of pregnant women in developing countries [6]. In Mumbai, India, for example, a food-based multiple-micronutrient supplement started preconceptionally and given throughout pregnancy halved the prevalence of maternal gestational diabetes [7]. Correction of specific vitamin deficiencies during pregnancy has improved outcomes for pregnant women and their babies in developed and developing country settings [8]. In a recent UK multi-centre trial of vitamin D supplementation during pregnancy, the Maternal Vitamin D Osteoporosis Study (MAVIDOS), supplementation corrected maternal vitamin D deficiency and optimised infant levels of vitamin D [9, 10].

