### 18–21 weeks gestation

Women attend at 18–21 weeks for a National Health Service (NHS) fetal anomaly scan and an additional high-resolution 3D ultrasound scan to obtain detailed measurements of their pregnancies. These scans are performed by the SPRING study sonographer. If any abnormalities are identified, women are referred to their local fetal medicine department for further management and might be excluded from this trial if the diagnosis would make it difficult for them to continue either with the IMP or the study procedures. The findings of any abnormal scans will be recorded as adverse events and thus might inform potential new hypotheses regarding the action of vitamin D in pregnancy. A pill count is performed to assess compliance with the study.

During the 18–21 weeks visit, and after the scan, the intervention research nurses hold a second Healthy Conversation with women in the Healthy Conversation Skills intervention groups to discuss their pregnancies, explore progress towards any goals they set at the 14 week visit and to set new ones if need be. Details of conversations are recorded on the Case Report Form. This forms part of the implementation component of process evaluation. Control research nurses give control group women an information sheet and confirm the timing of the 26 week phone call.

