#### Adverse drug reactions and adverse drug events

Any adverse event which might be linked in any way to vitamin D supplementation is immediately reported to the sponsor. A detailed written report on the event is produced. The principal investigator decides whether to expedite reports of adverse events felt to be unrelated to the IMP. A record of all serious adverse events is kept in the trial site file.

The sponsor keeps detailed records of all adverse events reported to them by the principal investigator. These records may then be sent to the licensing authority if required.

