### Data collection and management

To guarantee the validity and integrity of trial design and conduct, two committees are being established. The trial steering committee is overseeing trial design and implementation. An independent data monitoring committee is overseeing the data collection process.

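### The safety section rules out in advance any link between vitamin D and a list of serious pregnancy complications, and two reporting routes turn on that judgement

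*Protocol article*

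**What the plan says.** All references are to the protocol article.

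- **Anticipated adverse events.** The opening sentence is: "Some pregnancy-associated complications are expected to arise spontaneously during the study and are not associated with vitamin D supplementation". The events that follow include "gestational diabetes, pre-eclampsia, eclampsia, premature labour or delivery, instrumental delivery, Caesarean section, miscarriage or stillbirth", as well as cholestasis and pregnancy-induced hypertension. No source is cited.
- **Adverse drug reactions and adverse drug events.** The trigger for immediate reporting is a possible link: "Any adverse event which might be linked in any way to vitamin D supplementation is immediately reported to the sponsor". For the rest, "The principal investigator decides whether to expedite reports of adverse events felt to be unrelated to the IMP". The section adds that "A record of all serious adverse events is kept in the trial site file", and that the sponsor keeps records of the events which the principal investigator reports to it.
- **Suspected unexpected serious adverse reactions.** These go to the regulator and to the ethics and data monitoring committees within fixed times.
- **Data collection and management.** On the committee's role: "An independent data monitoring committee is overseeing the data collection process".
- **Study design** and **Randomisation.** The women, the research nurses and the research team are blind to the vitamin D allocation.

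**The concern.** It is reasonable to call these complications expected in a pregnant population. It is a different matter to state as fact that they have no association with the randomised product. Whether they occur more often on vitamin D than on placebo is a question that the trial's own comparison can inform, and the text answers it in advance.

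The wording matters because the reporting rules that follow rest on relatedness. An investigator who has been told that stillbirth or pre-eclampsia is unrelated has little ground to report it as possibly linked. What is at stake is safety surveillance of the vitamin D comparison during a recruitment period planned at up to 3 years. The efficacy analyses are not affected.

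**Working it through.** The plan gives no safety figure to reproduce, so the main check is a reading of the sections against each other.

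**Step 1. Follow a listed serious event, for example pre-eclampsia, through the stated routes.**

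| Route | Condition for entry | Status of a listed event under the opening sentence |
|---|---|---|
| Immediate report to sponsor | Possible link to vitamin D | Declared unlinked, so not triggered |
| Suspected unexpected serious reaction, to regulator and committees | Suspected of being related, and unexpected | Declared unrelated and expected, so it fails both conditions |
| Expedited report of an unrelated event | Principal investigator's decision | Possible, not required |
| Record in the trial site file | Serious | Recorded |

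The event is recorded, but neither route that is defined by relatedness is triggered. The wide test for a possible link and the blanket denial of a link cannot both be applied to the same event.

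**Step 2. Is the denial supported elsewhere in the article?** The safety evidence under Ethical considerations concerns asthma and atopy in the children. The Background says that an earlier vitamin D trial in pregnancy corrected maternal deficiency and optimised infant levels. Neither section gives rates of the listed complications by vitamin D group.

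**Step 3. Can individual judgement stand in for a comparison?** These complications occur without treatment. A blinded assessor who sees one case cannot know whether it belongs to an excess on one arm. Only counts by randomised arm can show that.

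**Step 4. What could counts by arm show?** This is an illustration. The complication rates and the doubling are assumptions, because the documents give none.

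- Group size: the recruitment target is 188 women in each of four arms (Sample size and power calculation). Each vitamin D comparison group is 2 × 188 = 376, and the total is 4 × 188 = 752.
- Expected events: 376 × p in one group and 376 × 2p in the other.
- Power, two-sided 5%: Φ[(|p₁ − p₂| − 1.96·SE₀)/SE₁], with SE₀ = √(2·p̄(1 − p̄)/376), SE₁ = √([p₁(1 − p₁) + p₂(1 − p₂)]/376) and p̄ the mean of p₁ and p₂.
- Worked case, 5% against 10%: SE₀ = √(0.13875/376) = 0.01921; SE₁ = √(0.1375/376) = 0.01912; (0.05 − 0.03765)/0.01912 = 0.646; power 0.74.

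| Assumed rates | Expected events | Power |
|---|---|---|
| 1% v 2% | about 4 v 8 | 20% |
| 3% v 6% | about 11 v 23 | 51% |
| 5% v 10% | about 19 v 38 | 74% |
| 8% v 16% | about 30 v 60 | 92% |

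For a smaller excess (ratio 1.5), power at baseline rates of 1%, 3%, 5% and 8% is 9%, 19%, 29% and 45%.

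**The case against.** The strongest reply is that one loose clause is being made to carry too much. The investigator's discretion concerns whether to expedite, not whether to report. All serious events are recorded. An independent data monitoring committee exists, and the trial has regulatory and ethics approval and is run under GCP. Periodic listings and tables by arm are commonly left by a journal article to the full protocol, the committee's charter or the analysis plan. The list may be meant only as a catalogue of background events, with relatedness still assessed for each case.

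Much of this stands, and it rules out several stronger readings that a reader might infer:

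- **That an excess in one arm would go unseen by the sponsor and the committee, or that nobody compares events by arm.** The article does not say so. Describing the committee as overseeing data collection neither states nor excludes review by arm.
- **That the Background contradicts the safety section.** The Background reports that "a food-based multiple-micronutrient supplement started preconceptionally and given throughout pregnancy halved the prevalence of maternal gestational diabetes", and gestational diabetes is on the list. That supplement contained multiple micronutrients and began before conception, so it does not test a statement about vitamin D alone.
- **That the fetal anomaly scan section contradicts it.** Abnormal scans are recorded because they "might inform potential new hypotheses regarding the action of vitamin D in pregnancy". They are not on the list. The section shows a more open stance on another type of event, not a conflict.
- **That no safety conclusion is possible for either intervention.** The disputed sentence concerns vitamin D only, so it says nothing about Healthy Conversation Skills. Serious events on file can still be tabulated by arm at the end.

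What the reply does not answer is the sentence itself. It is a positive assertion and not an omission, so detail in another document would not correct it. If relatedness is in fact assessed case by case, the sentence is wrong as an instruction to sites.

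**Conclusion.** The point holds in limited form. The safety section fixes causality in advance, without cited support, for a class of complications that includes serious ones, in a trial that randomises the product concerned. Read as written, it takes these events out of immediate reporting to the sponsor and out of the suspected-unexpected-reaction route. It remains unknown whether another route brings them to the sponsor and the committee, and the article does not establish that this fails.

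No figure in the plan is wrong on this point. The power values rest on assumed rates, an assumed doubling, full recruitment of 752 women and known outcomes for all of them. On those assumptions, a comparison by arm is informative for the commoner complications and weak for rare ones such as stillbirth. The change should be made because it is cheap and removes a prejudgement from safety surveillance.

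**What to change.** 1. **Anticipated adverse events:** delete the clause that denies any association with vitamin D. Describe the listed events as expected in pregnancy, and say that the relatedness of each is assessed under the adverse drug reactions section. Blinding is already in place, so no new safeguard is needed for that assessment.
2. **Reconcile the sections from Anticipated adverse events to Data collection and management**, so that they state how listed serious events reach the sponsor. Periodic line listings would suffice; expedited reports are not needed for this purpose.
3. **State that listed serious events are tabulated by coded vitamin D arm** for the data monitoring committee, and by arm in the final report. If the full protocol or the charter already provides for this, a cross-reference is enough.

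The cost is a wording amendment and one recurring table, built from records already kept and prepared by someone outside the blinded team. Dose, visits and efficacy analyses do not change. The committee should be told that counts of rare events will have low power, so that similar numbers in the two arms are not read as evidence of safety.
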